It is hypothesized that adolescents who are diagnosed with a severe eating disorder and are treated with olanzapine will demonstrate reduced disordered eating attitudes and behaviours as well as an increased rate of weight gain, as compared to a control group treated with placebo. It is also hypothesized that patients treated with olanzapine will demonstrate better long-term clinical outcomes in comparison to patients treated with placebo. It is also predicted that the adverse effects of olanzapine will be minor given the relatively low dose (as compared to treatment for patients with schizophrenia), slow titration, and short-term use of olanzapine.

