#### Secondary Outcome Measures

Change from baseline in the EAT-26 score measured at week 6, 15 (i.e. off medication) and at the end of the maintenance period (week 40), as well as BMI change measured at the same time points will be analyzed as for the primary outcomes. Change from baseline in the CAPI, the CDI, the MASC, the EDS3 and the CBCLwill be calculated for weeks 6, 12, 15 and 40.

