### Sample Size

Given the relative novelty of this application of olanzapine, no formal evaluation of the drug has yet been conducted on youth, making it difficult to accurately estimate sample size requirements. However, after consultation within our clinical team we believe that a decrease of 5 points on the EAT-26 scale would be clinically meaningful. The following assumptions were therefore used for sample size calculations: i) a minimal clinical important difference of 5 on the EAT-26 score; ii) an estimated standard deviation of 7.07; iii) two-sided test; iv) a power of 80% and a type I error of 5%; v) a provision for one interim analysis according to the O'Brien and Fleming criteria [35]. With these assumptions, the total sample size necessary is 64 participants. Anticipating a drop-out rate of at most 2.5%, the formula of Donner [36] may be used to adjust the sample size assuming an intention to treat analysis. The resulting total sample size is thus 67 participants (33 and 34 participants per treatment group). We anticipate that this study will take two years to complete enrollment.

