### Statistical Analysis

Descriptive summaries of demographic and treatment balance will be generated with respect to all participant characteristics at baseline. Dichotomous variables will be summarized using percentages, normally distributed continuous variables will be summarized using means together with standard deviations, and continuous variables that are not normally distributed will be summarized using medians together with range.

Statistical analysis of the data will follow the intention-to-treat principle for the main analysis of treatment outcomes. For participants who develop clinical events that will lead to withdrawal from the study, or that are lost to follow-up prior to the 12-week primary endpoint, we will use the BMI plus last value captured for the EAT-26 test as a method of imputation of missing data.

A student's t-test (assuming a normal distribution of the measures; otherwise, Wilcoxon Mann-Whitney test will be used) will be used in order to compute the change between the EAT-26 and the difference in BMI from baseline to week 12. If necessary, a linear regression model will be fit to assess treatment effect adjusting for variables thought to influence outcome that could result in imbalance between treatment groups at baseline. Treatment effect and its 95% confidence interval will be generated for each primary outcome.

To examine secondary outcomes, the differences between study groups will be assessed using Student's t-tests (as described above for primary outcome). In order to avoid multiple testing issues, results will be compared with an alpha value adjusted for the number of tests performed using the Bonferonni criterion.

Although the study is not powered to detect differences in safety, we will nevertheless compare the frequency of adverse events between the two study groups using chi-square or Fisher's exact test.

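### Plain Bonferroni over an unranked secondary family (26 tests on the literal reading) is valid but needlessly conservative; Holm's step-down gives the same error control and never rejects less

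*Protocol article*

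**What the plan says.** The Statistical Analysis section sets both the secondary test and its threshold: "To examine secondary outcomes, the differences between study groups will be assessed using Student's t-tests", and then "results will be compared with an alpha value adjusted for the number of tests performed using the Bonferonni criterion". It does not give the number of tests or rank any scale or visit.

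The Secondary Outcome Measures section lists what is to be tested. EAT-26 change is taken at weeks 6, 15 and 40, and "BMI change measured at the same time points will be analyzed as for the primary outcomes". For the other scales: "Change from baseline in the CAPI, the CDI, the MASC, the EDS3 and the CBCLwill be calculated for weeks 6, 12, 15 and 40".

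The Background states as a hypothesis that "patients treated with olanzapine will demonstrate better long-term clinical outcomes in comparison to patients treated with placebo". Week 40 is the only visit after week 15 in the Schedule of Events (Table 1), so the long-term hypothesis has to be judged there.

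The Sample Size section rests on EAT-26 alone, with "a minimal clinical important difference of 5 on the EAT-26 score". No power is claimed for any secondary outcome.

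**The concern.** Dividing alpha equally over every scale and visit sets a very strict threshold in a trial of 67. Visits on drug (week 6), off drug (week 15) and at follow-up (week 40) answer different questions but get the same share. Repeated visits of one scale in the same patients are also likely to be correlated, and Bonferroni then uses less than the 5% it is allowed. At stake is whether a secondary effect as large as the one the trial was sized for would be declared significant, at week 40 in particular. A method with the same protection and more power is available at no cost in patients or visits.

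**Working it through.** **Inputs.** Difference 5, SD 7.07, two-sided 5%, power 80%, 64 participants before and 67 (33 and 34) after drop-out (Sample Size); final alpha 0.048 (Interim analysis); scales and visits (Secondary Outcome Measures). *Assumption:* the standardised effect for EAT-26 applies to each secondary outcome. The protocol gives no effect sizes for them.

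**1. The plan's own figure.** n per arm = 2 × (1.960 + 0.842)² × (7.07/5)² = 2 × 7.85 × 2.00 = 31.4, so 32 per arm and 64 in total, as stated. 64/(1 − 0.025)² = 67.3, consistent with 67.

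**2. Number of tests, read literally.** EAT-26 and BMI: 2 × 3 = 6. CAPI, CDI, MASC, EDS3, CBCL: 5 × 4 = 20. Total 26.

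**3. Threshold.** 0.05/26 = 0.0019 (0.048/26 = 0.00185).

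**4. Power per test**, noncentral t, d = 5/7.07 = 0.707:

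| Per-test alpha | 32 per arm | 33 and 34 |
|---|---|---|
| 0.048 (unadjusted) | 79% | 81% |
| 0.05/7 = 0.0071 | 52% | 55% |
| 0.05/26 = 0.0019 | 35% | 38% |

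With 32 per arm, the noncentrality is 0.707 × √(32/2) = 2.83, and the critical t on 62 degrees of freedom is 3.24.

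**5. Other assumed effects at 0.0019, 32 per arm.** 0.3 SD: 3%. 0.5 SD: 12%. 0.8 SD: 49%. 1.0 SD: 77%.

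**6. Correlation.** The protocol gives none, so a range was simulated: 26 tests with a common correlation, normal approximation, 32 per arm. The last column is the power at the planning effect if the threshold were set to use the full 5%.

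| Assumed correlation | Actual familywise error under Bonferroni | Power at the threshold using the full 5% |
|---|---|---|
| 0 | 4.9% | 39% |
| 0.3 | 4.3% | 41% |
| 0.5 | 3.5% | 44% |
| 0.7 | 2.2% | 50% |
| 0.9 | 1.0% | 62% |

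**7. Holm on the same 26 tests.** Order the p-values and compare them in turn with 0.05/26, 0.05/25, 0.05/24 and so on, stopping at the first failure. If all 26 effects are 0.707 SD, average power per test is about 47–49% over these correlations, against 39% for Bonferroni on the same normal approximation. The gain comes only as tests are rejected: the second threshold is 0.05/25 = 0.0020, so the gain is smaller when few effects are real.

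**The case against.** - **Bonferroni is valid under any correlation.** This stands. Nothing is stated wrongly, and strictness on outcomes the trial was not sized for is a defensible stance. The point is one of efficiency.
- **The 26-test family is an inference.** This stands. The text says only that alpha is adjusted for the tests performed, and a statistical analysis plan not at hand may define a narrower family. The sentence sending EAT-26 and BMI back to the primary analysis could also be read as taking them out of the Bonferroni family. The later sentence on secondary outcomes points the other way. It is therefore not established that the long-term hypothesis is tested at 0.0019.
- **A reader might infer that the secondary hypotheses are almost untestable, or that the trial cannot answer its long-term question.** The figures do not support this. Power of 35–38% is low but not negligible, and it is 77% at 1.0 SD. Near-hopeless power appears only at about 0.5 SD or less.
- **A reader might blame correlation for most of the loss.** Up to a correlation of 0.5, a threshold using the full 5% lifts power only from 39% to 44%. Most of the loss comes from the number of tests.
- **Bonferroni has simple matching simultaneous confidence intervals and Holm does not.** True in general, but the Statistical Analysis section promises intervals only for the primary outcomes, so nothing planned is lost.
- **The 52–55% for seven tests is not a gain from Holm.** Correct. It comes from dropping 19 tests, which is a separate trade-off.

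**Conclusion.** The concern holds as a weakness of efficiency. On the literal reading, the secondary outcomes face 26 tests at about 0.0019 each. At the planning effect, each has about 35–38% power, against about 80% unadjusted, so an effect of that size would more often than not be declared non-significant. The week-40 tests have no priority over the other visits. Holm is better than the stated method on the same terms: equal familywise control under any dependence, and never fewer rejections.

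The size of the loss rests on two assumptions: that all listed scale-by-visit tests form one family, and that 0.707 SD carries over from week-12 EAT-26 to the other scales and visits. A narrower family would shrink the loss; smaller true effects would leave lower power.

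**What to change.** **Main change.** In Statistical Analysis, replace the Bonferroni criterion for secondary outcomes with Holm's step-down, and state which tests form the family and how many there are. This costs wording only. The first step stays at 0.0019 with 26 tests, so Holm recovers part of the loss and not all of it.

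**Optional, before unblinding.** Name a smaller key family that includes week 40. With seven tests, for example the seven outcomes at week 40, Holm's first step is 0.05/7 = 0.0071, with 52–55% power at the planning effect and looser thresholds at later steps. Report the remaining visits as estimates with confidence intervals. The cost is that those visits carry no formal claim. Choosing a different visit for some scales would leave those scales without a formal test at week 40, so the choice should follow from what the long-term hypothesis is meant to cover.

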In recent reviews of pharmacology and eating disorders, antipsychotic medications have demonstrated promise in the treatment of eating disorders. In spite of reported clinical success [14,18-20], and open trials: [21,22]), we are only aware of two published randomized controlled trials (RCT) which have evaluated the effectiveness of olanzapine [23,24]. The first of RCT contained a very small sample of adult patients with AN and compared the effects of olanzapine against chlorpromazine in reducing anorexic patients ruminating thoughts. Olanzapine was shown to be more effective than chlorpromazine in decreasing ruminative anorectic cognitions [23]. The second RCT investigated the effects of adding olanzapine treatment (randomized double blinded design) to patients participating in cognitive behavioral therapy. The number of patients in this study was also low, but psychological improvements were significant in the olanzapine group compared to the control group in specific cognitive domains. BMI's also significantly increased in the anorexic population with binge/purge subtype compared to the control group [24]. In recent case reports, olanzapine has been associated with considerable weight gain and maintenance, clinically notable decreases in levels of agitation, and improvements in sleep [14,18], general functioning, and overall compliance with treatment in children and adolescents diagnosed with AN [18,25,26].

Despite the lack of much empirical evidence, antipsychotic medications such as olanzapine are now widely used in the treatment of severe eating disorders. Recent case reports have demonstrated that olanzapine may be associated with marked improvements in weight gain, along with decreased anxiety and agitation, decreased obsessionality, and decreased resistance to treatment [14,18-22,25,26]. However, olanzapine will remain classified as an 'experimental' drug rather than a recommended and accepted treatment for AN, until safety and efficacy can be established in this population using a high quality randomized trial.

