### Trial Design

A randomized, double-blind, placebo-controlled design will be used to determine the efficacy and safety of olanzapine in treating AN. Consecutive female patients diagnosed with a severe eating disorder, who meet eligibility criteria, and who consent to participate in the study, will be randomly assigned to one of two groups: olanzapine (OLA) or placebo (PLA). A medication schedule will be in place for a total of 14 weeks (see Table 1 for Schedule of Events). Medication will be started at a low dose and increased up to a predetermined maximum dose, or until an intolerable side effect occurs. Both groups will receive either olanzapine or placebo for a total of 14 weeks. Both groups will continue to receive standard care that includes psychological, nutritional, and medical treatment.

**Table 1 T1:** Schedule of Events

Timelines + 3 days	Day -7	Day 0	Day 7	Day 14	Day 21	Day 28	Day 35	Day 42	Day 49	Day 56	Day 63	Day 70	Day 77	Day 84	Day 91	Day 98	Day 105	Day 280+ 7
VISIT	Screen	Week 0 Rand	Week 1	Week 2	Week 3	Week 4	Week 5	Week 6	Week 7	Week 8	Week 9	Week 10	Week 11	Week 12	Week 13	Week 14	Week 15 or Term	Week 40 F/UP

Informed Consent	x																	
Medical History	x																	
Demographics	x																	
Inclusion/Exclusion	x	x																
Height	x													x				x
Weight & BMI score	x	x	x	x	x	x	x	x	x	x	x	x	x	x	x	x	x	x
Physical Exam	x																x	
Randomization		x																
Vital Signs	x	x	x	x	x	x	x	x	x	x	x	x	x	x	x	x	x	x
Hematology & Chemistry*	x			x		x				x				x			x	
HBA1C				x													x	
Multistick Urinalysis	x	x	x	x	x	x	x	x	x	x	x	x	x	x	x	x	x	
Urine for Pregnancy	x	x	x	x	x	x	x	x	x	x	x	x	x	x	x	x	x	
Electrocardiogram (EKG)	x			x		x											x	
Adverse Events			x	x	x	x	x	x	x	x	x	x	x	x	x	x	x	x
Concomittant Meds (mg)	x	1.25 → 2.5	5	7.5	7.5	7.5	7.5	7.5	7.5	7.5	7.5	7.5	7.5	5.0	2.5	0	0	0
Dispense Study Med		x	x	x	x	x	x	x	x	x	x	x	x	x	x			
AIMS			x	x	x	x	x	x	x	x	x	x	x	x	x	x	x	
Psychological Measures																		
EAT-26		x						x						x			x	x
CDI **		x						x						x			x	x
MASC **		x						x						x			x	x
CAPI		x						x						x			x	x
CBCL**		x						x						x			x	x
EDS3		x						x						x			x	x

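### The between-arm safety analysis is an underpowered test of difference with no stated interval, so a null result could not support the prediction that harms are minor

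*Protocol article*

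**What the plan says.** Safety is one of the questions put to the trial. Trial Design states: "A randomized, double-blind, placebo-controlled design will be used to determine the efficacy and safety of olanzapine in treating AN". Safety Issues likewise says that assessments at each visit serve to determine the drug's safety. The hypotheses at the end of the Background add an expectation about the answer: "It is also predicted that the adverse effects of olanzapine will be minor given the relatively low dose".

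For the comparison between arms, Statistical Analysis names one method, in a sentence that opens with a concession: "Although the study is not powered to detect differences in safety, we will nevertheless compare the frequency of adverse events between the two study groups". The tests it names for this are chi-square or Fisher's exact. Earlier in the same section interval estimation is promised, but for efficacy: "Treatment effect and its 95% confidence interval will be generated for each primary outcome". No interval, margin or excluded risk is mentioned for adverse events. The Data Safety and Monitoring Committee section describes a blinded safety tabulation, and Interim analysis a look at safety issues. Neither names another between-arm method.

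**The concern.** The question and the method point in different directions. The prediction is that harm is small. Chi-square and Fisher tests take no difference as the null hypothesis, so a significant result can speak against the prediction, but a non-significant one only fails to reject. With about 33 patients per arm, non-rejection is also the more likely outcome of Fisher's test under many moderate excesses. A comparison of frequencies also says little about severity, which is what the word minor concerns.

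At stake is how informative the safety result will be. A p-value alone does not show how much excess harm the data leave open. For an antipsychotic given to underweight girls aged 12 to 17, that is what a reader most needs to know.

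**Working it through.** **Inputs from the protocol article.** Sample Size: difference of 5 EAT-26 points, SD 7.07, two-sided 5%, power 80%, dropout 2.5%, total 64 before and 67 after dropout, arms of 33 and 34. **Assumed:** olanzapine is the arm of 34; the safety alpha is 0.05, because none is stated; all event risks, because none are given.

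**1. The plan's own sample size.** n per arm = 2 × [7.07 × (1.960 + 0.842) / 5]² = 31.4, rounded up to 32, so 64 in total. For dropout, 64 / (1 − 0.025)² = 67.3, which agrees with 67. The arm sizes can be used as stated. They were set by EAT-26, not by safety.

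**2. Power of the planned safety test.** Let a and b be the numbers of patients with an event in the olanzapine and placebo arms. Power = sum, over all tables (a, b) with p < 0.05, of Bin(a; 34, olanzapine risk) × Bin(b; 33, placebo risk). The miss rate is 1 − power.

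| Placebo vs olanzapine risk (assumed) | Fisher power | Fisher miss | Chi-square (uncorrected) power | Chi-square miss |
|---|---|---|---|---|
| 5% vs 10% | 3% | 97% | 11% | 89% |
| 5% vs 15% | 13% | 87% | 26% | 74% |
| 10% vs 20% | 13% | 87% | 21% | 79% |
| 5% vs 20% | 32% | 68% | 46% | 54% |
| 10% vs 30% | 45% | 55% | 56% | 44% |
| 20% vs 40% | 36% | 64% | 44% | 56% |
| 30% vs 50% | 34% | 66% | 38% | 62% |
| 20% vs 60% | 92% | 8% | 93% | 7% |

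**3. Smallest excess found with 80% power by Fisher's test.** Olanzapine risk of 23% against 0%, 33% against 5%, 41% against 10% and 54% against 20%. These are absolute excesses of 23, 28, 31 and 34 points.

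**4. What an interval would show that the p-value hides.** Take 7/34 against 2/33 as an illustration. The risks are 20.6% and 6.1%, the difference is 14.5 points, and Fisher p = 0.15. The Wilson 95% limits are 10.3% to 36.8% and 1.7% to 19.6%. Newcombe's method combines them:
- lower limit = 0.1453 − √[(0.2059 − 0.1035)² + (0.1961 − 0.0606)²] = −0.025
- upper limit = 0.1453 + √[(0.3680 − 0.2059)² + (0.0606 − 0.0168)²] = +0.313

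So a non-significant test sits alongside an interval from about −2.5 to +31.3 points. Smaller counts behave in the same way: 3/34 against 1/33 gives p = 0.61 with −7.8 to +20.1 points, and 5/34 against 2/33 gives p = 0.43 with −7.2 to +24.7 points.

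**5. Zero events.** The upper limit of the exact two-sided 95% interval for 0/34 is 1 − 0.025^(1/34) = 10.3%. Seeing no event of a given type still leaves a true risk of about one in ten open.

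**The case against.** The strongest reply is that the article claims nothing false. It admits the lack of power in the very sentence that names the test. A reader might infer that a non-significant p will be taken as proof of safety, but no section states such a rule, margin or success criterion. A reader might also infer that the trial claims it will establish safety. Trial Design says only determine, the remark about minor effects is a prediction, and "until safety and efficacy can be established in this population using a high quality randomized trial" is Background text on when the drug would cease to be classed as experimental. These replies stand, and the point does not depend on either inference.

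The magnitude rests on assumed risks, so it cannot be said that most relevant harms would be missed. Large excesses of common events would be found (20% against 60% in 92% of trials), and chi-square detects 10% against 30% in 56%. This stands too; the supported statement concerns moderate excesses.

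A condensed article may leave safety detail to the full protocol or analysis plan. That holds for between-arm analyses of laboratory values, EKG and AIMS, which are not part of this point. It does not dispose of the adverse event comparison: the article names the method and, in the same section, reserves intervals for the primary outcomes. Finally, comparing frequencies implies that counts per arm will be available. That is true, and it is why the change costs almost nothing.

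**Conclusion.** The concern holds in a limited form. Safety is an aim and harms are predicted to be minor, but the between-arm method that the article fixes can only contradict that prediction. At 34 against 33, Fisher's test misses 55% to 97% of the assumed excesses of 5 to 20 points, and uncorrected chi-square 44% to 89%. Fisher reaches 80% power only for excesses of about 23 points (from 0%) to 34 points (from 20%). A null result therefore could not support the prediction, although the article does not say that it will be read that way. The percentages depend on assumed event risks and a two-sided 0.05 level. The logical point, that failing to find a difference is not evidence of little harm, depends on neither. The primary efficacy analysis and the sample size are unaffected. This is a cheap improvement to a stated method, not an error that threatens the trial.

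**What to change.** In Statistical Analysis, make estimation the between-arm safety analysis:

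1. For patients with any adverse event, with any serious adverse event and with each event type (by severity where recorded), report the risk in each arm and the risk difference with a 95% confidence interval, for example Newcombe's.
2. Where an arm has no events of a type, give the exact upper bound on its risk.
3. Keep the chi-square or Fisher p-values as descriptive only, and say that any statement that harms are minor will rest on the upper confidence limits and not on non-significance.

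The cost is analysis wording: no extra patients, visits or measurements. The small downside is that the intervals will be wide and will show that sizeable excess harm cannot be ruled out, so the safety statement becomes less favourable.

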### Data Safety and Monitoring Committee

This study will be monitored by an independent DSMC formed by the steering committee. The present DSMC consists of three individuals who are not involved in this research trial: a psychologist specializing in Mental Health Research, an adolescent psychiatrist specializing in psychopharmacology, and a pediatrician specializing in drug trials (RCTs of chemotherapy in cancer patients). A statistician who is blind to the treatment allocation will conduct a tabulation of safety data, and participants' baseline characteristics after one year of recruitment. The committee will be made aware by the study coordinator of any concerning side effects, and all data will be reviewed after the enrollment of the tenth participant. Members of the DSMC will also be responsible for developing terms of reference including clinical stopping rules and examples of data presentation to be used for the tabulation of the data for the safety analysis. The steering committee will be notified by the DSMC only if the latter considers continuance of the study to be unacceptable.

